### Interventions

#### Intervention arm: TI-MBCT

The intervention will be group-based TI-MBCT developed through the intervention refinement phase of the study (see Table 3). The focus of this intervention is creating a new relationship with trauma-related phenomena and learning how to respond when the trauma of the past shows up in the present. TI-MBCT addresses the re-experiencing and reactivity characteristic of people who have experienced DVA with PTSD through the gradual development of skills for “de-centering” from distress. Instead of avoiding or becoming overwhelmed by distressing thoughts, powerful impulses, intense feelings, and disturbing body sensations, participants gradually learn to approach such experiences without judgment and with more acceptance and to gently ask “given that this experience is happening right now, how can I best take care of myself?” The cultivation of a non-judgemental attitude to what is arising in the present moment enables a way of responding, rather than reacting, to the self when trauma-related distress is experienced. In addition, being part of a group allows for a recognition that distress arising from past abuse is a shared experience, which reduces the sense of identification with being “damaged” that many people who have experienced DVA feel ([name]: How can an adapted MBCT course meet the specific vulnerabilities of women survivors of domestic violence and abuse? Unpublished thesis: Bangor University; 2015).

**Table 3 Tab3:** TI-MBCT intervention overview

TIDieR* item	Description
Brief name	Trauma informed mindfulness-based cognitive therapy (TI-MBCT) [58, 59]
Why	TI-MBCT addresses the patterns of avoidance, re-experiencing, and reactivity characteristic of people who have experienced DVA with PTSD through the gradual development of skills for managing overwhelm and developing skills for “decentering” from distress
What	The manual, mindfulness practices and exercises for TI-MBCT will be developed through the intervention refinement process.
Who provided	An experienced mindfulness teacher with expertise in trauma, who is in supervision with a mindfulness-based supervisor with expertise in trauma.
How	TI-MBCT delivered in face-to-face groups of up to nine participants
Where	A site will be selected which is safe and convenient for both participants and the therapist (e.g., community centre).
When and how much	Once a week for eight weeks participants will attend a 2-h session and conduct 45 min of guided home practice.
Tailoring	The intervention will be refined to meet the needs of women with DVA trauma with a particular emphasis on establishing a sense of safety from which to turn towards challenging experiences.
Modifications	TI-MBCT will be refined during the study based on evidence synthesis from 1. A literature review on trauma-sensitive adaptations of mindfulness-based interventions 2. Qualitative interviews with women who have experienced DVA (including feasibility trial participants) and professional stakeholders 3. Consensus exercise with “experts by experience” of delivering mindfulness-based interventions to participants who have experienced trauma.
How well Planned Actual	Therapists’ records will be analysed to measure intervention uptake, retention and dose received. Home practice records completed by participants will be analysed to measure dose received. A standard tool for assessing fidelity of a mindfulness-based intervention [60] will be adapted to the TI-MBCT course and tested in the feasibility trial.

Note: *TI-MBCT* trauma-informed mindfulness-based cognitive therapy, *DVA* domestic violence and abuse

*Template for Intervention Description and Replication (TIDieR) checklist [61]

#### Control arm

Participants in the control group will be self-referred to the local IAPT service. Participants accessing the IAPT service receive an initial telephone assessment, after which they are offered different forms of therapy, based on the nature and severity of their symptoms and the availability of practitioners. At 6-month follow-up, we will collect IAPT data regarding each control participant’s individual care pathway to understand what psychological intervention(s) are provided as usual care.

### Outcomes and measures

The outcome of the *intervention refinement* component will be stakeholder views on the content and format for the TI-MBCT refinement obtained through semi-structured qualitative interviews.

#### Feasibility outcomes

Table 4 summarizes feasibility outcomes that will be used in the *feasibility trial* to evaluate the feasibility of a future full-size trial.

**Table 4 Tab4:** Feasibility outcomes

Outcome	Description; measure
Recruitment/randomization rate	Proportion of participants randomized into two arms; the denominator will be the number of participants eligible for recruitment/randomization
Intervention uptake	Proportion of participants who took up the TI-MBCT or self-referred to the IAPT service; the denominator will be the number of participants randomized in the arm, respectively.
Intervention retention	Proportion of participants in the intervention arm who received the “minimum dose” of the intervention, four sessions of mindfulness intervention [29].
Follow-up rate	Proportion of participants followed up and providing outcome data at six months post-randomization out of those enrolled in the trial. The proportion who have been lost to follow-up will also be calculated by the trial arms.
Participant experience	Participant views on the acceptability of the intervention and trial design.

#### Intervention impact outcomes

Trial participants will complete standardized validated and bespoke questionnaires at baseline and 6-month face-to-face meetings with study researcher (Table 2). If we find that it is feasible and acceptable to collect the intervention impact data, these outcomes will be used in a full-size trial. The primary outcome will be clinically important symptoms of PTSD [21] captured by self-administered PTSD Checklist for DSM-V (PCL-5) [44] and International Trauma Questionnaire (ITQ) [45]. Secondary outcomes will include the severity of dissociative symptoms, depression, anxiety, DVA re-victimization, self-compassion, and woman reported child health and wellbeing.

#### Economic measures

A resource use data collection form will be developed for the trial, informed by that used in the Psychological Advocacy Towards Healing trial [56]. EQ-5D-5L will be used to collect data on participant health-related quality of life [50]. Responses will be converted to utility scores using the standard UK tariff values and this used to estimate quality-adjusted life years.

### Data collection methods

#### Intervention refinement

Qualitative data will be collected during semi-structured interviews with stakeholder professionals and women who have experienced DVA. Researchers will collect brief sociodemographic data (professional role/employment status, age, gender, ethnicity) at the outset, then use flexible topic guides to ensure primary issues are covered during each interview. Topic guides will be modified as necessary to address emerging findings and new lines of enquiry. A participant distress protocol will guide researchers during interviews about how to respond if participants become distressed during or after the interviews. Researchers will be supervised and have access to debriefing following participant interviews.

#### Feasibility trial

Data regarding feasibility will be obtained from study logs of recruitment and follow-up, therapists’ records about intervention uptake/sessions attended, retention and dose received, and interviews with participants about the acceptability of the intervention and trial design. Clinical data will be collected at face-to-face meetings with the researcher using the standardized validated questionnaires listed above. Economic data will be collated from the study logs detailing the cost of intervention delivery. Self-reported economic measures will be collected from participants 6 months post-randomization using paper-based, self-completed, and interviewer-assisted questionnaires.

### Data analysis

#### Qualitative analysis

Interview audio-recordings will be professionally transcribed and imported into NVivo software for line-by-line coding. The framework method [62] will be used to analyze the data in order to identify themes across the dataset, using constant comparison techniques. A second researcher will be involved in coding and reviewing themes. Data from the feasibility trial will first be analyzed as two separate data sets (intervention and control arms) to look at common themes within each arm, before making analytic comparisons across the data sets. Data will be explored for disconfirming cases within and across the arms of the study.

Data will be analyzed at two time points; initially after the first intervention group, in order to inform any further refinements of the prototype and subsequently, after the second intervention group to make comparisons across the two groups and time points, in terms of delivery and content of the intervention and the control group experience.

#### Quantitative analysis

Since this is a feasibility trial, the statistical analyses are mainly descriptive. We will calculate rates with 95% confidence intervals (CIs). Medians (ranges) will be calculated for ordinal data, means with standard deviations (SD) for continuous data, and raw counts (number, %) for nominal data. Differences in means (and 95% confidence intervals) between the two study arms will be presented for the various outcome scales, but no *p* values will be displayed. The SD of the outcome measures will be used to help inform a sample size calculation for a full trial.

#### Economic evaluation

The aim of the economic analysis is to inform the design of economic evaluation in the full-scale trial. The feasibility trial will be used to determine the optimal perspective, type of economic evaluation, scope, and data collection methods. The research team will design data collection tools, aiming to minimize missing data and identify relevant unit costs and the main cost drivers. The costs of the intervention and the control treatment will be crucial. An aim will be to establish how best to collect the data and how to value it.

Descriptive statistics will be reported for all quantitative and economic data collected. Missing data will be examined between baseline and follow-up interviews and prior to a full trial, with a view to establishing causes of missing data and how these might be addressed.

### Withdrawal criteria

Participants may withdraw because they no longer wish to attend the intervention or control therapy or assessment meetings or because a change in their health status or personal circumstances warrants their withdrawal. Researchers will attempt to contact participants up to three times using different modalities (e.g., text, email, and phone), before deeming them to be lost to follow-up. Data obtained up to the point of withdrawal will be anonymized and retained for analysis. Participants who have withdrawn or dropped out of the study will be contacted once by telephone and asked if they would agree to answer some questions to explore the reasons for their non-participation. This will be explained in the participant information sheet and consent form.

It is hoped that participants withdrawing from the intervention or control arm would remain willing to participate in follow-up measurements at 6 months; all participants withdrawing from the intervention/control phase will be approached once at the 6-month point, but contact will not be pursued if participants either (i) indicate that they do not wish to complete the follow-up stage or (ii) do not respond.

In the circumstance that a participant wishes to withdraw from the trial and therapy completely, they will no longer receive contact from the mindfulness teacher (if in the intervention arm), or from the IAPT therapist (if in the control arm) and will not be contacted about follow-up research appointments.

### Data management

Quantitative data will be entered in REDCap software. STATA will be used to conduct statistical analyses and produce graphs. Qualitative interviews will be audio-recorded on a University of Bristol approved encrypted digital recorder, transcribed, and analyzed in NVivo software. Information collected by the mindfulness teacher/IAPT therapist about the progression of the intervention will be recorded separately in the teacher/therapist logbook, and in pre-specified tables and worksheets.

We will follow the University of Bristol Data Protection Policy built on the General Data Protection Regulation. Personal data will be kept in a secure place—electronically in the study folder on the departmental file store with password-protected access and hard copies in a locked cabinet in a locked room on secure university premises. Personal data and an anonymization log will be kept separately from research data, and participants will be identifiable by study ID.

After the study has concluded, we will deposit the anonymized data in the University of Bristol Data Repository. Analyzed data will be retained for a minimum of 10 years.

### Study organization and management

The sponsor (University of Bristol) and funders (see below) had no role in the design of this study and will play no role in its conduct, data analysis, and interpretation, manuscript writing, or dissemination of results. The sponsor and funder will not control the final decision regarding any of these aspects of the study. The study management group (SMG) will assist the principal investigator in the day-to-day management of the project and meet monthly. A joint study steering committee and data monitoring and ethics committee (SSC/DMEC) of independent experts in DVA, PTSD, mindfulness, and statistics will act as an advisory group. The study is conducted in collaboration with a patient and public involvement (PPI) group consisting of women who have experienced DVA, who will advise on study materials and processes.

The study is conducted in accordance with the Research Governance Framework for Health and Social Care and Good Clinical Practice. The study will be monitored and audited in accordance with sponsor policies. All feasibility trial-related documents will be made available on request for monitoring and audit. Amendments to the protocol will be submitted to the Research Ethics Committee for approval.

### Adverse event reporting

All adverse events will be reported from the time the participant is enrolled in the feasibility trial until completion of the last study-related procedure. The research team will collect data on adverse events from study participants, researchers, and interventionists. Participants will be asked about adverse events at least every 30 days. If an adverse event were to occur, the study investigator or a delegated member of the study team would assess whether the event is serious or unexpected, and whether it is likely to be related to the study procedures or interventions. All adverse events will be recorded in the study file with a note that will identify when the event occurred, what happened, any potential study relation, action taken and resolution/closure of the adverse event. All serious adverse events will be reported to the University of Bristol research governance and ethics officer, who will notify the relevant Research Ethics Committee, the Insurance Office and the Research Governance Team as appropriate.

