Allocation concealment will be achieved using the remote randomization service acting as a “third party” to assign the participant to either intervention or control arms. This ensures that the study researcher, enrolling and consenting participants, cannot be influenced by knowledge of their expected allocation at this stage. Once the participant has been allocated to either the intervention or the control arm, this assignment will be made available to the researcher. This is to enable the participant’s details to be passed onto the mindfulness teacher if they are in the intervention arm. The mindfulness teacher will invite the prospective intervention participants to an orientation meeting followed by an individual telephone assessment. Those participants randomized to the control arm will be advised by the study investigator how to self-refer to the IAPT service and helped with the self-referral if needed and wanted.

Due to the psychological nature of the intervention in both trial arms, it will not be possible to blind participants to details of which arm they have been allocated. Due to funding limitations, the same study researcher will carry out recruitment, baseline, and follow-up assessments, and monthly check-up calls; therefore, it will not be possible to blind the study investigator to the treatment groups. All process evaluation and analysis will be conducted by a different researcher blind to the participation group.

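### Adverse events come partly from interventionists, contact with whom differs by arm, and the source is not among the listed record items, so any summary by arm may be inflated in TI-MBCT

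*Protocol article*

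**What the plan says.** The Adverse event reporting section names three sources: "The research team will collect data on adverse events from study participants, researchers, and interventionists". It adds a systematic enquiry: "Participants will be asked about adverse events at least every 30 days". Each record is to hold the timing, a description, any possible relation to the study, the action taken and the resolution. Who reported the event is not on that list.

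In the TI-MBCT arm, the Recruitment and consent section says: "The mindfulness teacher will invite the prospective intervention participants to an orientation meeting followed by an individual telephone assessment". Table 3 sets the course: "Once a week for eight weeks participants will attend a 2-h session and conduct 45 min of guided home practice".

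For the control arm, the protocol says: "Participants in the control group will be self-referred to the local IAPT service". What follows depends on symptoms and on which practitioners are available. Two flows of IAPT information are described. The Control arm section says: "At 6-month follow-up, we will collect IAPT data regarding each control participant’s individual care pathway". The Data management section says: "Information collected by the mindfulness teacher/IAPT therapist about the progression of the intervention will be recorded separately in the teacher/therapist logbook". Neither is described as a route for adverse events.

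One researcher, who is not blinded, covers both arms: "the same study researcher will carry out recruitment, baseline, and follow-up assessments, and monthly check-up calls".

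**The concern.** Of the three sources, the participant enquiry and the researcher's calls are not limited to one arm. The interventionist source is different. The TI-MBCT teacher belongs to the trial and sees the women on a fixed schedule. The IAPT therapist works in an outside service, delivers care that the trial does not set, and may never be reached. Self-referral to IAPT is itself an uptake outcome in Table 4, so the protocol does not take that contact for granted.

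If two arms have the same true event rate but one has an extra channel through which events are noticed, that arm tends to record more events. A reader of a safety table by arm could not then tell a real excess from better detection. Without the source on each record, the two may not be separable afterwards. This matters because the trial is meant to inform a definitive trial, and an independent joint steering and data monitoring committee advises on it.

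**Working it through.** The protocol gives no adverse event rate, count or comparison by arm, so there is no stated figure to reproduce. The check asks how large a difference unequal detection alone could produce.

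**Inputs from the protocol**
- Scheduled teacher contacts in TI-MBCT: 1 orientation meeting + 1 telephone assessment + 8 sessions = 10.
- Follow-up: 6 months, about 26 weeks, with about six 30-day enquiries in each arm (182/30 ≈ 6).
- Share of follow-up with teacher contact: f = 8/26 = 0.308 for the course alone. Allowing two further weeks for the pre-course contacts (an assumption), f = 10/26 = 0.385.
- Pre-start drop-out: of every 18 randomized at 2:1, 12 go to TI-MBCT and 6 to control. Eight and four are expected to continue. 8/12 = 4/6 = 2/3, so the expected loss is one third in each arm.

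**Assumptions, none given in the protocol**
- s: chance that an event is captured at the 30-day enquiry, the same in both arms; 0.4, 0.6 or 0.8.
- t: chance that the teacher picks up an otherwise missed event arising in the teacher-contact weeks; 0.3 to 0.7.
- No events reported by IAPT therapists, and events spread evenly over follow-up.

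**Step 1. All TI-MBCT women have teacher contact.** Detection is s in control and s + (1 − s)·f·t in TI-MBCT. With equal true rates, the apparent ratio is 1 + [(1 − s)/s]·f·t. The product f·t runs from 0.308 × 0.3 = 0.092 to 0.385 × 0.7 = 0.269.

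| s | (1 − s)/s | Apparent ratio |
|---|---|---|
| 0.4 | 1.50 | 1.14 to 1.40 |
| 0.6 | 0.667 | 1.06 to 1.18 |
| 0.8 | 0.25 | 1.02 to 1.07 |

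**Step 2. Apply the pre-start drop-out.** If women who leave before the start have no teacher contact, the excess per randomized woman is two thirds of that in step 1.
- s = 0.4: 2/3 × 13.8% = 9% to 2/3 × 40.4% = 27%.
- s = 0.6: 2/3 × 6.2% = 4% to 2/3 × 17.9% = 12%.
- s = 0.8: 2/3 × 2.3% = 1.5% to 2/3 × 6.7% = 4.5%.

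For s between 0.4 and 0.6, the range is therefore about 4% to 27%.

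**Step 3. Let IAPT therapists report too.** A second model, without the limit to course weeks, lets the teacher catch an event with probability q and the IAPT therapist with probability qc, each independently of the enquiry. The ratio is [1 − (1 − s)(1 − q)]/[1 − (1 − s)(1 − qc)]. With s = 0.8 and q = 0.5:
- qc = 0: 0.90/0.80 = 1.125.
- qc = 0.25: 0.90/0.85 = 1.06.
- qc = 0.5: 0.90/0.90 = 1.00.

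The ratio is also 1.00 whenever s = 1. An inflation in TI-MBCT needs both q > qc and s < 1.

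**Step 4. Raw counts.** Under 2:1 allocation, equal event rates already give about twice as many events in TI-MBCT, so raw counts by arm cannot be compared in any case.

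**The case against.** The strongest objection is that the protocol plans no comparison of adverse events by arm. They are absent from the progression criteria (Table 1) and the feasibility outcomes (Table 4). The Quantitative analysis section is mainly descriptive, and the Adverse event reporting section sets out review of individual events. How events are tabulated may properly be left to the full protocol or the analysis plan. This stands: the point concerns what any such summary would inherit, and does not show that a stated analysis is biased.

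Second, the term interventionists is not confined to the mindfulness teacher, and the Data management section names the IAPT therapist as a record-keeper. Zero reporting from IAPT is thus an inference. That also stands. Even so, the gap closes only if IAPT detection matches the teacher's or the common enquiry misses nothing, and nothing in the text assures either.

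Third, teacher contacts are not enquiries. Most are group sessions of up to nine women, nothing says that events are asked about there, and part attendance would lower detection further. This bears on size and leaves the inequality of contact in place.

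Two stronger readings are tempting. A reader might infer that counts by arm will overstate harm in TI-MBCT and that the direction is certain. The document does not support this: the direction depends on the teacher detecting more than IAPT therapists do, and on equal reporting at the 30-day enquiry. A reader might also take the expected loss of two in every six controls as a further imbalance. The same sentence implies a loss of four in every twelve in TI-MBCT, which is the same fraction.

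**Conclusion.** The point holds in a limited form. Scheduled interventionist contact is unequal by design, no adverse event route is described for IAPT therapists, and the source of a report is not among the listed record items. A safety summary by arm may therefore be inflated in TI-MBCT relative to IAPT.

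The size cannot be settled from the document. It is nil under equal IAPT reporting or complete capture at the 30-day enquiry, and a few per cent if the enquiry captures 80%. The range of roughly 4% to 27% per randomized woman rests on 40% to 60% capture at the enquiry, 30% to 70% pick-up by the teacher, no IAPT reporting, and no teacher contact for the third expected to leave before the start. All but the drop-out fraction are assumptions about reporting that the protocol does not supply. The change is worth making because it is cheap and the source may not be recoverable later.

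**What to change.** Keep collecting events from every source, so that safety action is unchanged. Add a field to the adverse event record for who first reported the event: participant at the 30-day enquiry, teacher, IAPT or researcher.

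State that any between-arm comparison will use per-woman rates or proportions of events elicited at the 30-day enquiry, asked in the same words in both arms, and will not use raw counts. List events first reported by the teacher, IAPT or the researcher separately, by arm.

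The cost is one form field, set before data collection, and one sentence in the analysis text. The small downside is that the comparison rests on fewer events. It also remains an enquiry by an unblinded researcher, which this change does not address.
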